### Domain-level evaluation

At the domain level, Kruskal-Wallis H-test with Bonferroni correction will be used to compare median values across groups. This analysis is conducted for each domain variable to assess differences between AI chatbots. [20] Furthermore, we will evaluate the frequency of responses crossing critical thresholds—such as “insufficiently verified facts” in the factual consistency domain, or “substantially incoherent” in the coherence domain. Prevalence ratios will be computed to compare incidence rates between different generated responses. [21]

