## Materials and methods

This project aims to evaluate the potential role of AI chatbots to assist clinicians by providing immediate analysis and suggestions to enhance and augment clinical practice and workflow. The protocol employs a universal standardised prompt template to compare between AI chatbot responses against real-life clinical scenarios. Generated responses will be evaluated by a panel of practicing clinicians [specialists (n =  3); resident trainees (n =  3)] using a 5-point Likert scale. [6] Human evaluators will serve as domain experts with specific knowledge in clinical microbiology and virology, as well as internal medicine and clinical infectious diseases (Fig 1).

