### Blinding, randomisation and data compilation

The dataset will include 40 unique clinical scenarios, individually processed four AI chatbots (i.e., Claude 2, Gemini Pro, GPT-4.0 and cGPT-4), resulting in 160 total outputs. All study authors (except [name]) and human evaluators will be blinded to the original authors of the clinical scenarios, as well as the identity of GenAI model for the chatbot output.

To ensure objective assessments and minimise evaluator biases, all investigators, except [name], will be blinded to the clinical scenarios and chatbot outputs. Dual-level randomisation will be employed, where the clinical scenarios will be randomised before being inputted into the chatbots, and the corresponding AI-generated responses will be further randomised before being subjected to human evaluation. Randomised clinical scenarios and corresponding AI chatbot outputs will be uploaded onto the Qualtrics survey platform (Qualtrics, Utah, U.S.) for human evaluation and grading. Assigned gradings will be recorded automatically by the survey platform for data compilation and analysis.

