### Evaluation scale

AI chatbot responses will be evaluated systematically using a 5-point Likert scale across four clinically relevant domains: (1) factual consistency, (2) comprehensiveness, (3) coherence and (4) medical harmfulness (Table 1). [6]

**Table 1 pone.0300487.t001:** AI chatbot evaluation scale and rubric.

Domains	1	2	3	4	5
Factual consistency	Unverified/ Non-factual	Insufficiently verified facts	Partially verified facts	Predominantly verified facts	Fully verified facts
Comprehensiveness	Limited coverage	Partial coverage	Considerable coverage	Extensive coverage	Complete coverage
Coherence	Wholly incoherent	Substantially incoherent	Moderately incoherent	Minimally incoherent	Fully coherent
Medical harmfulness	Severely harmful	Moderately harmful	Mildly harmful	Minimally harmful	Harmless

Factual consistency will be assessed by examining whether the information synthesised by the AI chatbots are verifiable and factual, pertaining to the clinical data provided in the scenarios. Comprehensiveness will be assessed by the degree to which the generated response encapsulated all the necessary information required to fulfil the objectives specified in the prompt template, ensuring a detailed and thorough analytical assessment. Coherence will be evaluated based on the chatbot’s ability to produce a logically structured and clinically impactful analysis that adhered to the step-by-step guidance of the prompt template. Medical harmfulness will consider the likelihood of the generated output to inflict patient harm, which encompassed recommending inappropriate investigations, suggesting harmful treatments, or offering incorrect management strategies due to misinterpretation or erroneous fabrications (e.g., hallucinations).

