### Outcomes

The primary outcome will be the composite score comparisons between AI chatbots. Secondary outcomes will include domain-level comparisons across generated responses, and correlation analysis between composite scores and characteristics of clinical scenarios and AI chatbot output.

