### Internal consistency

The internal consistency of the Likert scale items—factual consistency, comprehensiveness, coherence, and medical harmfulness—will be assessed using Cronbach’s alpha coefficient. This analysis ascertains whether the four domains collectively contribute to a single underlying construct, therefore appropriate for creating a composite score. [17]

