### Statistical significance

A p-value of less than 0.05 will be considered statistically significant.

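### Domain-level comparisons use single-step Bonferroni; Holm's step-down rule in the same family keeps the 5% familywise guarantee and can detect more

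*Protocol article*

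**What the plan says.** Under Outcomes, the domain results are a secondary outcome: "Secondary outcomes will include domain-level comparisons across generated responses". The Evaluation scale section lists four domains: "1) factual consistency, (2) comprehensiveness, (3) coherence and (4) medical harmfulness". The Domain-level evaluation section fixes both the test and the adjustment: "At the domain level, Kruskal-Wallis H-test with Bonferroni correction will be used to compare median values across groups", and adds "This analysis is conducted for each domain variable to assess differences between AI chatbots". The significance level comes from the Statistical significance section: "A p-value of less than 0.05 will be considered statistically significant".

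The correction is named without a step-down version. The article does not say which set of tests it spans. It states no power, effect size or adjusted significance level for these comparisons.

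**The concern.** Single-step Bonferroni holds every test in a family of m to 0.05/m, even after some hypotheses have been rejected. Holm relaxes the threshold after each rejection and still limits the chance of any false rejection to 5%, whatever the dependence between tests. The usual reason to prefer Bonferroni is that it yields simple simultaneous confidence intervals. That has little force here, because the section plans Kruskal-Wallis tests and describes no such intervals.

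At stake is power for a named secondary outcome that includes medical harmfulness. If chatbots differ in several domains, or one chatbot stands apart from the other three, some of those differences can go undeclared although a rule with the same familywise guarantee would have declared them.

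**Working it through.** **Inputs from the article.** Four domains; four chatbots; 40 scenarios each answered by all four chatbots, "resulting in 160 total outputs"; alpha 0.05. There is no stated power or adjusted alpha to reproduce.

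**Possible families.** Four omnibus tests (m = 4); 4 × 3 / 2 = 6 chatbot pairs within a domain (m = 6); 4 × 6 = 24 pairs in all (m = 24).

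**Why a correction is useful.** For independent tests, familywise error is 1 − (1 − a)^m.
- m = 4: 1 − 0.95^4 = 0.185 unadjusted; 1 − (1 − 0.0125)^4 = 0.0491 with Bonferroni.
- m = 6: 1 − 0.95^6 = 0.265 unadjusted; 1 − (1 − 0.05/6)^6 = 0.0490 with Bonferroni.

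**Thresholds.** Holm compares the i-th smallest p-value with 0.05/(m − i + 1) and stops at the first failure. For m = 4 the steps are 0.05/4 = 0.0125, 0.05/3 = 0.0167, 0.05/2 = 0.025 and 0.05. Bonferroni uses 0.0125 throughout. Two facts follow without any simulation:
- No Holm threshold is below 0.05/m, so Holm rejects whatever Bonferroni rejects.
- The first step is the same, so the chance of at least one rejection is identical.

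**Size, four-domain family (assumed effects).** Kruskal-Wallis per domain, 40 responses per chatbot.

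*Evenly spaced chatbot means, all four domains differing, domain correlation 0.5, 3,000 runs per setting:*

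| Span of means (SD) | Power per domain, Bonferroni → Holm | All four found |
|---|---|---|
| 0.5 | 25% → 31% | 5% → 13% |
| 0.6 | 39% → 47% | 12% → 25% |
| 0.7 | 56% → 66% | 24% → 46% |
| 0.8 | 73% → 82% | 43% → 66% |

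A separate run at 0.7 SD gave 57% → 65% per domain and 24% → 44% for all four.

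*One chatbot shifted, domain correlation 0.6, scores on a 1/6-point grid (mean of six raters), no scenario correlation, 1,000 runs per setting:*
- All four domains differ: 0.353 → 0.431 at 0.5 SD; 0.734 → 0.817 at 0.7 SD; 0.944 → 0.973 at 0.9 SD, where power is near its ceiling.
- Two domains differ by 0.7 SD: 0.761 → 0.777. With an assumed scenario correlation of 0.3 or 0.5: 0.731 → 0.751 and 0.754 → 0.780.
- One domain differs by 0.7 SD: 0.722 → 0.723.

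**Error check (same one-chatbot setting).** With no true differences both rules gave 0.053, against a simulation standard error of √(0.05 × 0.95 / 1000) = 0.007. With two domains differing, familywise error was 0.016 for Bonferroni and 0.039 for Holm.

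**Size, six-pair family (assumed effects).** Dunn tests within one domain, 2,000 runs per setting. Chatbot means are in SD units:
- (0, 0, 0, 0.7): 0.623 → 0.655 average power per true pair.
- (0, 0, 0.7, 0.7): 0.625 → 0.677.
- (0, 0.35, 0.7, 1.05): 0.420 → 0.459.

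In this family a lone false hypothesis cannot occur: if one chatbot differs from the other three, three pairs differ.

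**The case against.** The strongest reply is that nothing here is wrong. Bonferroni is a valid, conservative rule, the outcome is secondary, and no power is claimed that could be contradicted. That stands, and it limits the point to an efficiency gain.

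Three further objections also stand, at least in part.

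- **The family is open.** A reader might infer that every domain test is held to 0.0125. The article does not say so. The correction may instead apply to the six pairs within a domain, parallel to ANOVA with Tukey for the composite score. Each omnibus test would then run at 0.05, and Holm across the four domains would add a correction and lower omnibus power. The four-domain figures above hold only for the four-domain reading. Holm's advantage over Bonferroni within the same family holds on every reading.
- **The plan does not predict that all four domains differ.** A reader might infer this from the Internal consistency section. That section describes a check still to be made: "This analysis ascertains whether the four domains collectively contribute to a single underlying construct". Correlated items also do not imply that chatbot means differ on each item. The all-four case is therefore the favourable one.
- **Holm is less strict in one respect.** With one domain truly null and three differing (evenly spaced means, 0.7 SD), error for the null domain was 0.9% with Bonferroni and 3.1% with Holm, while power in the other three was 57% and 62%. Bonferroni also limits the expected number of false rejections to 0.05, which Holm does not. The article does not invoke that stricter property, and for familywise error nothing is given up.

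One might add that an unpaired test on matched scenarios can cost more power than the adjustment does. That is a separate question. Holm's advantage does not depend on which test supplies the p-values.

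**Conclusion.** The point holds as a free improvement. For any fixed family, Holm gives the same 5% familywise guarantee as Bonferroni, never rejects less, and rejects more in some samples when more than one hypothesis is false. That part needs no assumptions.

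The size does. With n = 40 per chatbot, a four-domain family and moderate assumed differences, the gain is roughly 5 to 10 points of per-domain power if all four domains differ, 2 to 3 points if two differ, and none if one differs. It shrinks once power is already very high. For six pairs within a domain, the three patterns tried gave about 3 to 5 points. The chance of at least one rejection does not change.

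A reader might go further and conclude that the plan's adjustment is faulty, or that it will miss real domain differences. The document supports neither: Bonferroni controls the error, and whether anything is missed depends on effects that are not known. The supported statement is that differences can be missed.

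**What to change.** In the Domain-level evaluation section, replace the Bonferroni correction by a *Holm step-down adjustment*, applied to the family that the Bonferroni correction was meant to cover. Name that family in the same sentence: the four domain omnibus tests, the six chatbot pairs within a domain, or all 24 pairs. Report adjusted p-values. The article condenses a longer plan that may already define the family; if so, carry that definition over.

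Two cautions apply:
- Do not stack layers by default. With Holm across the four domains and then Holm at the full 5% among six pairs in each significant domain, simulated familywise error over all 24 pairs was 6.3% to 11.0% (one chatbot shifted 0.9 to 1.5 SD in all domains, domain correlation 0 to 0.5, Dunn tests, 4,000 runs). Bonferroni over all 24 gave 0.5% to 1.3%. Claim control over 24 pairs only if Holm is run over all 24. Within-domain Bonferroni would not give that control either.
- Make the change before domain results by chatbot are seen. The timeline section places preliminary analysis in March 2024 and final analysis by May 2024. If results are already known, keep Bonferroni as planned and label any Holm result as additional.

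The cost is one sentence, with no new data. Holm has no simple matching simultaneous confidence intervals, but the article plans none for these tests.

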### Human evaluation

Two groups of human evaluators will be invited to conduct the study. Human evaluators will be selected from the Department of Microbiology at the University of Hong Kong, the Department of Medicine (Infectious Disease Unit) at QMH, and the Department of Medicine & Geriatrics (Infectious Disease Unit) at Princess Margaret Hospital. The first group will consist of three specialists while the second group will include three resident trainees. These two panels of evaluators will be representative of a diverse range of clinical experience and expertise, therefore offering a broad spectrum of insights into the analytical performance of AI chatbots in the clinical setting.

The evaluators will be presented with the clinical scenarios in random order along with the corresponding AI chatbot-generated responses, which will also be anonymised. Evaluators will be blinded to the identity of AI chatbots during the evaluation process. They will be instructed to read the entire clinical scenario and each of the generated responses in full, before grading. Blinded evaluations will be conducted independently during the evaluation period.

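### The domain comparisons use Kruskal-Wallis, a test for independent groups, on chatbot scores matched by scenario and rater, so the nominal 5% level is not delivered

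*Protocol article*

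**What the plan says.** The Domain-level evaluation section of the protocol article names the test: "Kruskal-Wallis H-test with Bonferroni correction will be used to compare median values across groups". It then fixes what is compared: "This analysis is conducted for each domain variable to assess differences between AI chatbots". The Outcomes section makes these comparisons a secondary outcome.

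The design is set out elsewhere in the article. Under Blinding, randomisation and data compilation: "The dataset will include 40 unique clinical scenarios, individually processed four AI chatbots", "resulting in 160 total outputs". Under Materials and methods, grading is by a "panel of practicing clinicians [specialists (n = 3); resident trainees (n = 3)] using a 5-point Likert scale". Under Human evaluation: "They will be instructed to read the entire clinical scenario and each of the generated responses in full, before grading". The significance rule is "A p-value of less than 0.05 will be considered statistically significant".

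No blocked, repeated-measures or mixed method is named for the domains. The only paired method in the article is the paired t-test in Composite score evaluation, and that compares specialist with non-specialist evaluators, not chatbots. On thresholds, the article says only "Prevalence ratios will be computed to compare incidence rates between different generated responses".

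**The concern.** Kruskal-Wallis takes its null distribution from independent observations in independent groups. Here each scenario contributes one output to every chatbot, so a hard case tends to lower all four scores together, and a strict rater lowers them all too. The test counts this shared variation as noise, although it cancels when chatbots are compared on the same cases. If single ratings are pooled, a second problem pulls the other way: six ratings of one output are not six independent pieces of evidence about that chatbot.

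The description is also inexact. Kruskal-Wallis responds to rank ordering, and on a 5-point scale medians will often tie.

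At stake are the separate conclusions on factual consistency, comprehensiveness, coherence and harmfulness. A test with little power could miss a real difference in harmfulness, and readers may take that as equal safety. An inflated test could report differences that are not there.

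**Working it through.** **Inputs from the article.** 40 scenarios, 4 chatbots, 6 evaluators, a 5-point scale, threshold 0.05.

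**The article's own figure.** 40 × 4 = 160 outputs, as stated. If every evaluator grades every output, which is how the text reads, there are 160 × 6 = 960 ratings per domain and 960 / 4 = 240 per chatbot.

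**Assumed inputs.** The article gives no variance components. Each rating is taken as a latent normal score with total variance 1, split into scenario (S), rater (R), scenario-by-chatbot output (O) and residual (E). It is cut at −2.0, −1.25, −0.4 and 0.7 to give five levels.

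**Expected direction.** On the latent scale, compare the variance that truly affects chatbot differences with the variance that the test assumes:

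- Output means: (O + E/6) / (S + O + E/6). This is below 1 whenever S is positive, so the test is conservative.
- Pooled ratings: (6·O + E) / (S + R + O + E). This can fall on either side of 1.

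For S, R, O, E = 0.2, 0.2, 0.2, 0.4, the first is (0.2 + 0.067) / (0.2 + 0.2 + 0.067) = 0.57 and the second is (1.2 + 0.4) / 1 = 1.60.

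**Simulation with no chatbot difference**, 3,000 runs per setting, rejection rate at nominal 0.05 (KW = Kruskal-Wallis):

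| S, R, O, E | Ratio, means | KW, 160 means | Ratio, ratings | KW, 960 ratings | Friedman by scenario |
|---|---|---|---|---|---|
| 0, 0, 0, 1 (control) | 1.00 | 0.048 | 1.00 | 0.051 | 0.050 |
| 0.3, 0, 0, 0.7 | 0.28 | 0.000 | 0.70 | 0.017 | 0.055 |
| 0.3, 0.2, 0, 0.5 | 0.22 | 0.000 | 0.50 | 0.004 | 0.048 |
| 0.5, 0.1, 0, 0.4 | 0.12 | 0.000 | 0.40 | 0.003 | 0.046 |
| 0.4, 0.2, 0.05, 0.35 | 0.21 | 0.000 | 0.65 | 0.016 | 0.052 |
| 0.3, 0.2, 0.1, 0.4 | 0.36 | 0.000 | 1.00 | 0.061 | 0.048 |
| 0.2, 0.2, 0.2, 0.4 | 0.57 | 0.006 | 1.60 | 0.169 | 0.051 |
| 0.1, 0.2, 0.3, 0.4 | 0.79 | 0.023 | 2.20 | 0.290 | 0.045 |
| 0, 0.2, 0.3, 0.5 | 1.00 | 0.053 | 2.30 | 0.318 | 0.049 |

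The control row recovers 5% for all three tests, so departures elsewhere come from the matching and clustering. The simulated sizes follow the ratios.

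**Power**, one chatbot shifted by 0.25 latent SD:

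| S, R, O, E | KW, 160 means | Friedman |
|---|---|---|
| 0.3, 0.2, 0.1, 0.4 | 0.148 | 0.644 |
| 0.2, 0.2, 0.2, 0.4 | 0.204 | 0.425 |
| 0.4, 0.2, 0.05, 0.35 | 0.064 | 0.805 |

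Kruskal-Wallis on the 960 ratings rejects in about 0.75 of runs in all three settings, but at true sizes of 0.061, 0.169 and 0.016, so that power does not come with a controlled level.

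A further simulation, again with assumed shares and scenario variance present, used a 0.3-SD shift. Power was 0.20–0.50 for Kruskal-Wallis on output means and 0.51–0.83 for Friedman. The size of Kruskal-Wallis was 0.000–0.020 on means and 0.035 to about 0.30 on pooled ratings.

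**Medians.** Three chatbots were given probabilities 0, 0.1, 0.2, 0.6, 0.1 over scores 1 to 5, and the fourth 0, 0, 0.1, 0.45, 0.45. All four medians are 4. With 240 independent ratings per chatbot, Kruskal-Wallis rejected in 100% of runs. A significant result is therefore no evidence that the medians differ.

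**The case against.** The strongest reply is that the article is condensed and a fuller plan may handle the matching. That would answer an omission, but here a specific test is named for a specific comparison, and a fuller plan could correct it only by contradicting the published text.

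Other parts of the reply do stand:

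- **Direction.** A reader might infer that the domain tests will produce false positives. The documents do not support that. On output means the error is conservative, and about nominal if scenarios do not differ. On pooled ratings it goes either way. The article fixes neither the unit of analysis nor the variance shares.
- **Prevalence ratios.** A reader might infer that these are wrong too, treating 240 ratings per chatbot as independent. The article states no test, interval, variance method or unit, and a condensed article may leave these to the full plan. In this balanced design the ratio is valid as a point estimate. A design effect of 1 + 5 × ICC (2 to 3 for an assumed ICC of 0.2 to 0.4) would overstate the error, because it ignores the positive covariance between chatbots that share scenarios and raters. In the simulated settings above, an independent-sample test of the ratio, if one were used, rejected in 0.016 to 0.123 of runs.
- **Medians.** Comparing medians is common shorthand and holds under a pure location shift. This is a wording error. It does not make the test blind to differences between groups with equal medians; the test detects them.
- **Rank.** These are secondary outcomes.

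**Conclusion.** The point holds for the Kruskal-Wallis test. The article specifies an independent-samples test for scores matched by scenario and, as described, by rater, and the 5% level is not delivered in nearly all the settings examined. With scenario variance present, which is to be expected among consecutive real referrals, the test on 160 output means has a true size of about 0 to 2% and loses much of its power: about 0.2–0.5 against 0.5–0.8 for Friedman at a 0.3-SD shift. On 960 pooled ratings the type I error runs from under 1% to about 30%, driven by the scenario-by-chatbot share. That the test does not fit the design follows from the article alone. Every percentage rests on assumed variance shares and on all six evaluators grading all outputs. The median wording should be corrected. No error is established for the prevalence ratios. The change should be made before the domain results are reported.

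**What to change.** For each domain, average the six ratings of each output and compare the four chatbots with a Friedman test blocked by scenario. Follow with paired Wilcoxon tests under Bonferroni. An ordinal mixed model with scenario, output and rater effects is an acceptable alternative, but Friedman is enough.

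In the same edit, state the unit of analysis and what the Bonferroni correction covers: 0.05 / 4 = 0.0125 for the four domains, 0.05 / 6 = 0.0083 for the six chatbot pairs within a domain, or 0.05 / 24 = 0.0021 for all pairs in all domains. Describe results as differences in score distribution or rank ordering, not in medians. If intervals are reported for the prevalence ratios, cluster them on scenario.

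The cost is analysis wording and code. No new data, outputs or gradings are needed.
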